### Sample size

Sample size was determined based on the pilot data on two outcome measures and based on the requirement of the statistical methods that will be used to test the objectives. The primary outcome is the mobility gains score, the difference between mobility scores at discharge and at admission. In the Pilot Project at Toronto Rehab [32], the mean mobility gains score was 12.0 with a standard deviation of 5.7. This effect size was large: 2.1. The mean mobility gains score is expected to be higher for the PCRM-CI group than for the usual care group. If we assume that the mean mobility gains score for the usual care group will be 7.2 and the mean mobility gains score for the PCRM-CI group will be 12.1, with a common standard deviation of 5.7, the sample size estimate is 23 patients with an alpha of 0.05, power of 80% and a two sided *t*-test. In the Pilot Project, a secondary outcome was the rate of return to the community, which was 80% for patients with CI, and the PCRM-CI group is expected to maintain this rate. One can estimate that the rate of return to the community in the Usual Care group is about 50%. For comparison of these two proportions, with an alpha of 0.05 and power at 80%, the sample size estimate is 39 patients for each of the Usual Care and PCRM-CI groups. In order to allow for attrition, our goal will be to recruit additional patients beyond the minimums for a sample size of 140 patients (70 patients in each cohort).

Previous recruitment rates for evaluation studies have indicated that most staff are willing to participate. A sample size of 35 staff was estimated as sufficient to demonstrate changes in HCPs’ attitudes, based on results from the pilot project.

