### Data collection

Ethics approval was obtained at the sites and the RAs (one at each site) have been trained in data collection procedures by the PI and a clinical psychologist for the cognitive scales (MMSE, CAM, Delirium Index, and IQCODE) and by a co-investigator for the FIM scale. The RAs have also been trained to conduct interviews, to take field notes and to record factors that may influence the adoption of the model into practice. Each RA is responsible for recruitment, data collection, and data management for one institution.

The study is running at the same time in both facilities. Staff have been asked to participate within the first few months of the project. Recruitment of patients in the usual care group has taken one year. Following this period, the workshop developed in phase 1 was given to all HCPs on the unit. The criteria for admissions were then revised to allow a larger number of community dwelling patients with CI to be admitted. Eight additional educational sessions, described earlier, have been given to the staff during a three-month learning period. Recruitment of patients for the PCRM-CI model of care has commenced, and accrual will take 8 months.

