### Data analysis

Objective #1: The primary objective is to determine the impact of PCRM-CI on improvements in mobility (FIM locomotion and mobility) at discharge. At each site and for Usual Care and PCRM-CI groups, mobility is to be assessed at entry into rehab and at discharge from rehab. The change scores for patient outcomes will be compared with paired t-tests by cohort and site. In secondary analyses, multivariate regression will be used to examine the independent effects of each independent variable of interest on patient outcomes while controlling for other predictors and patient baseline factors**.**

Objective #2 (1 & 2): In the second instance, the mobility and physical functioning change scores and return to prior residence for Usual Care patients will be compared to those for PCRM-CI patients to assess the relative impact of the PCRM-CI model on outcomes for each site. Cross tabulations will be employed to assess rates of return to residence by rehab program and site. In particular, patients with CI are to be specifically targeted in the PCRM-CI model. We will compare means of mobility and physical functioning gains scores for patients with and without CI by program and site to assess the relative impact of the PCRM-CI model on patients with CI. In secondary analyses, multivariate regression will be used to examine the independent effects of each independent variable of interest on patient outcomes while controlling for other predictors and patient baseline factors**.**

Objective #2 (3): The introduction of the PCRM-CI model on the two units is meant to a) improve HCPs’ knowledge and attitudes toward working with hip fracture patients with CI, and b) measure the impact on provider satisfaction and work stress of working with these patients.

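### The primary cohort contrast is an unadjusted FIMM gain in non-equivalent cohorts, so differences in admission mobility and CI mix can move it by an unknown amount in either direction

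*Protocol article*

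**What the plan says.** The Sample size section defines the primary endpoint: "The primary outcome is the mobility gains score, the difference between mobility scores at discharge and at admission". It sizes the study on a two-group comparison of that gain, assuming that "the mean mobility gains score for the usual care group will be 7.2" and that "the mean mobility gains score for the PCRM-CI group will be 12.1, with a common standard deviation of 5.7".

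Under Data analysis, Objective #1, the stated method is: "The change scores for patient outcomes will be compared with paired t-tests by cohort and site". No covariate enters. Regression that controls for baseline factors is placed among the secondary analyses, and admission FIMM is not named there. The explicit comparison of Usual Care with PCRM-CI patients comes only in the next paragraph, under Objective #2, again on change scores.

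Methods/Design describes the design as non-equivalent, quasi-experimental and before-after. The Data collection section says that, after the usual-care year and the staff workshop: "The criteria for admissions were then revised to allow a larger number of community dwelling patients with CI to be admitted". Table 2 schedules FIM mobility and locomotion at admission and discharge, and MMSE, the Confusion Assessment Method and IQCODE at admission.

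**The concern.** A raw gain score gives the admission score a fixed coefficient of 1. If the slope of discharge on admission FIMM within a cohort differs from 1, a gap in starting level between cohorts becomes a gap in mean gain even when the model of care does nothing. Randomisation would keep such gaps to chance. Here nothing does, and the sponsor changed the intake between the two periods.

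The intake change also shifts CI mix directly. The Background section names CI and low pre-fracture function as the leading predictors of poor walking prognosis. The unadjusted contrast can thus be displaced by two features of the patients, both measured at admission. At stake is whether the headline difference can be read as an effect of the model or partly reflects who was admitted.

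The named test adds to this. A paired t-test within a cohort and site asks whether those patients changed between admission and discharge. It cannot compare two independent cohorts, so the primary contrast is not pinned to any between-cohort analysis.

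**Working it through.** **Inputs from the Protocol article (Sample size).** Pilot: "the mean mobility gains score was 12.0 with a standard deviation of 5.7". Planning means are 7.2 and 12.1, so the difference is 12.1 − 7.2 = 4.9, with common SD 5.7. Target: "a sample size of 140 patients (70 patients in each cohort").

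**Reproducing the plan's figure.** The article states that "the sample size estimate is 23 patients with an alpha of 0.05, power of 80% and a two sided" t-test is used. The normal approximation gives 2 × [5.7 × (1.960 + 0.842) / 4.9]² = 21.2, or 22 per group. The exact two-sample t gives power 79.5% at 22 and 81.4% at 23. The stated 23 is therefore reproduced as a per-group number for a two-sample t-test, which is not the paired test named under Data analysis. At 70 per cohort the same assumptions give about 99.9% power.

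**Standard error of the gain contrast.** 5.7 × √(2/70) = 0.963.

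**Shift from unequal admission FIMM.** Let D be the number of points by which the PCRM-CI cohort starts lower and b the within-cohort slope of discharge on admission FIMM. Suppose the cohorts would have equal discharge scores, given admission score, without the model. The gain contrast is then displaced by (1 − b) × D. The documents give neither D nor b, so both are assumed.

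| D | b | Shift in gain contrast | Share of 4.9 | Two-sided rejection with no effect (nominal 5%) |
|---|---|---|---|---|
| 2 | 0.3 | 1.4 | 29% | 30% |
| 2 | 0.5 | 1.0 | 20% | 17.8% |
| 2 | 0.7 | 0.6 | 12% | 9.5% |
| 4 | 0.5 | 2.0 | 41% | 54.0% |
| 4 | 0.7 | 1.2 | 24% | 23.5% |

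The last column uses a two-sample t-test on gains (138 df, SE 0.963). This is the test implied by the sample size, not the paired test named in the analysis section. If the PCRM-CI cohort starts higher, every sign reverses.

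**Shift from CI mix.** If patients with CI gain less than others at the same admission score, the contrast also moves by −(rise in CI share) × (shortfall in gain with CI). Neither factor is given. The sign opposes the rows above, so the net displacement could be positive, near zero or negative.

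**The mirror case.** Suppose instead that the cohorts would have had equal gains without the model. The raw gain contrast is then unbiased. A model adjusting for admission FIMM is displaced by −D − b × (−D) = −(1 − b) × D, which is −1.0 at D = 2 and b = 0.5. With equal SDs and correlation 0.5, the adjusted SE is 0.963 × √0.75 = 0.834, and false rejection is about 22%.

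**Precision.** With equal SDs at admission and discharge and correlation ρ (assumed), the variance ratio of adjusted to gain analysis is (1 + ρ)/2. This is 0.65, 0.75 and 0.85 at ρ = 0.3, 0.5 and 0.7, and the SE falls to 0.777, 0.834 and 0.888. Imbalance takes some of that back: a 1 SD gap in admission FIMM inflates the adjusted variance by 1.25, giving a net ratio of 0.75 × 1.25 = 0.94 at ρ = 0.5 and 0.85 × 1.25 = 1.06 at ρ = 0.7.

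**The case against.** The strongest reply is that baseline adjustment is not neutral in non-randomised cohorts. Whether the gain score or the adjusted model is biased depends on what would have happened without the model, and the data cannot settle that. As the mirror case shows, the adjusted model can err by the same amount in the opposite direction. This stands, and it is why both analyses should be reported.

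A reader might infer from the widened criteria that PCRM-CI patients start lower and that the raw gain therefore flatters the model. The documents do not support that. They report no admission FIMM, slope or correlation for either cohort, and more CI could depress gains.

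A reader might also infer a serious loss of precision. On the plan's own assumptions power is about 99.9%, so any gain in precision is a minor side benefit, and large imbalance can erase it.

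Further, the planned secondary regression may well include admission FIMM, and its covariate list may sit in the full protocol. That softens the point, but the article itself makes the unadjusted gain primary. Finally, the primary objective concerns patients with CI. If the contrast were restricted to them, the change in CI share would matter less. Data analysis, Objective #1, states no such restriction, and severity of CI could still differ.

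**Conclusion.** The point holds as a weakness in how the primary contrast is fixed. An unadjusted gain in sequential, non-equivalent cohorts with a deliberately changed intake leaves the main result open to differences in admission mobility and CI mix. The illustrative size is 0.6 to 1.4 points for a 2-point lower start and slopes of 0.7 to 0.3. It rests entirely on those assumed values and on the cohorts being otherwise comparable given admission score. The actual direction and size are unknown, so the documents show exposure to bias, not a demonstrated bias in favour of PCRM-CI. It is also clear from the text that paired t-tests by cohort and site do not deliver a between-cohort comparison.

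**What to change.** Make the primary analysis a linear model of discharge FIMM on cohort, with admission FIMM, site and CI status at admission as covariates. Report the adjusted cohort difference with its 95% CI, in place of the paired t-tests by cohort and site. State the rule that classifies CI from the admission instruments. Keep the unadjusted two-sample difference in gains, with its 95% CI, as a prespecified sensitivity analysis. Say plainly that the two rest on different assumptions and that agreement between them is reassuring but not proof against confounding.

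All the variables are already collected, so the change needs no new visits or patients. The real cost is procedural. Data on the 70 controls are in and 45 intervention patients are enrolled, so this is a mid-study change to the primary analysis. It should be dated, justified and recorded before the cohorts are compared.

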### Data analysis

Objective #1: The primary objective is to determine the impact of PCRM-CI on improvements in mobility (FIM locomotion and mobility) at discharge. At each site and for Usual Care and PCRM-CI groups, mobility is to be assessed at entry into rehab and at discharge from rehab. The change scores for patient outcomes will be compared with paired t-tests by cohort and site. In secondary analyses, multivariate regression will be used to examine the independent effects of each independent variable of interest on patient outcomes while controlling for other predictors and patient baseline factors**.**

Objective #2 (1 & 2): In the second instance, the mobility and physical functioning change scores and return to prior residence for Usual Care patients will be compared to those for PCRM-CI patients to assess the relative impact of the PCRM-CI model on outcomes for each site. Cross tabulations will be employed to assess rates of return to residence by rehab program and site. In particular, patients with CI are to be specifically targeted in the PCRM-CI model. We will compare means of mobility and physical functioning gains scores for patients with and without CI by program and site to assess the relative impact of the PCRM-CI model on patients with CI. In secondary analyses, multivariate regression will be used to examine the independent effects of each independent variable of interest on patient outcomes while controlling for other predictors and patient baseline factors**.**

Objective #2 (3): The introduction of the PCRM-CI model on the two units is meant to a) improve HCPs’ knowledge and attitudes toward working with hip fracture patients with CI, and b) measure the impact on provider satisfaction and work stress of working with these patients.

To meet this objective, descriptive statistics and paired t-tests analyses will be used for assessing the effects of the PCRM-CI model on provider experiences. Finally, the investigators will combine the qualitative assessments of HCPs in evaluating the impact of the PCRM-CI. Data pertaining to APN, HCPs and unit manager (interview and focus group transcripts, education log, field notes and treatment checklist) will be analyzed. Using an organizing/categorizing approach, each piece of qualitative data will be compared with every other piece of relevant data to develop insights into evidence, context and facilitation. The first step consists of reviewing all of the data sets and breaking the data down into discrete parts that are subsequently compared for similarities and differences (open-coding). The second step consists of putting the data together in new ways, by making connections between categories. The final step consists of systematically relating core categories to other categories, in order to integrate or refine analysis (selective coding). All the data sets will be reviewed to validate the core concepts [57].

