**Methods/Design:**

A non-equivalent pre-post design is being used to evaluate the PCRM-CI compared to usual care. All community dwelling (private home or retirement home) patients following a hip fracture are eligible to participate. Recruitment of both cohorts is taking place at two facilities. Target accrual is 70 hip fracture patients in the PCRM-CI cohort and 70 patients in the usual care cohort. We are also recruiting 70 health care providers (HCPs), who are being trained to implement the PCRM-CI, and their unit managers. Patient data are collected at baseline, discharge, and 6 months post-discharge from an inpatient rehabilitation program. Evaluations include mobility, physical function, and living arrangement. Additional outcome variables are being collected from medical records and from the patients *via* their proxies. Data on the prevalence and severity of dementia and delirium are being collected. Staff data are collected at baseline and one year after implementation of the model to determine change in staff knowledge and attitudes toward patients with hip fracture and CI. Bi-monthly semi-structured interviews with unit managers have been conducted to examine factors and barriers influencing the model implementation. Data collection began in 2009 and is expected to be completed in 2012. The control cohort of 70 patients has been recruited, and 45 patients have been accrued to the intervention group to date.

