## Methods/Design

A non-equivalent quasi-experimental before-after design is being used. Two sites have agreed to participate in the study. Multi-site sampling increases robustness by allowing for an assessment of comparisons and contrasts between the sites. Patient outcomes will be assessed at the time of discharge from inpatient rehabilitation and 6 months after discharge in cohorts of patients at both sites before and after implementation of the PCRM-CI model. The study has been registered at http://clinicaltrials.gov, Identifier NCT01566136.

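### The primary objective is assigned paired t-tests, which on either reading do not validly compare PCRM-CI with usual care and which conflict with the two-group sample size calculation

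*Protocol article*

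**What the plan says.** The Abstract sets the comparison: "A non-equivalent pre-post design is being used to evaluate the PCRM-CI compared to usual care". The Methods/Design section says that outcomes are assessed "in cohorts of patients at both sites before and after implementation of the PCRM-CI model", so the two groups are separate sets of patients. No matching is described.

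The Sample size section defines the endpoint: "The primary outcome is the mobility gains score, the difference between mobility scores at discharge and at admission". It states the expected direction, "The mean mobility gains score is expected to be higher for the PCRM-CI group than for the usual care group", and plans for mean gains of 7.2 and 12.1 with a common SD of 5.7, a two-sided t-test, alpha 0.05 and 80% power, giving 23 patients.

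The Data analysis section, Objective #1, restates the aim: "The primary objective is to determine the impact of PCRM-CI on improvements in mobility (FIM locomotion and mobility) at discharge". It notes that mobility is measured at entry and at discharge in each group and site, and then gives the test: "The change scores for patient outcomes will be compared with paired t-tests by cohort and site". Multivariate regression follows as a secondary analysis.

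The next paragraph, Objective #2 (1 & 2), holds the explicit comparison of the two programs. It begins: "In the second instance, the mobility and physical functioning change scores and return to prior residence for Usual Care patients will be compared". The other side of this comparison is the PCRM-CI cohort, and it is made for each site. That paragraph does not name a test for the comparison of mean gains.

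**The concern.** The study asks whether PCRM-CI gives more mobility than usual care. A paired t-test needs two measurements on the same patient or on matched patients. Here the only natural pairs are admission and discharge within a patient, and a test on those pairs asks whether patients recover during rehabilitation. The protocol itself expects substantial recovery under usual care. The test named for the primary objective therefore either answers a different question or is applied to data without pairs. The comparison that does answer the question is placed second and split by site.

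At stake is what is reported as the primary result. If the section is followed as written, the headline analysis may be a set of within-cohort p-values that say nothing about the contribution of the model.

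**Working it through.** **Inputs (Sample size section).** Usual-care gain 7.2; PCRM-CI gain 12.1; SD of the gain 5.7; two-sided alpha 0.05; power 80%; stated size 23; planned enrolment 70 per cohort. The article gives no split by site, so 35 per cohort per site is an assumption.

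**Step 1. Which test produces 23?**
- Standardised difference: d = (12.1 − 7.2)/5.7 = 4.9/5.7 = 0.86.
- Independent groups, normal approximation: n = 2(1.960 + 0.842)²/d² = 2 × 7.85/0.739 = 21.2, so 22 per group.
- Independent two-sample t-test (noncentral t): n = 22.24, so 23 per group. Power is 79.5% at 22 and 81.4% at 23.
- Paired or one-sample t-test at the same d: n = 12.7, so 13.

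The stated 23 is reproduced by the independent two-sample t-test and not by a paired one.

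**Step 2. Reading A: paired tests within each cohort and site.** Suppose PCRM-CI adds nothing, so that its cohort also gains 7.2 (SD 5.7). The standardised gain is 7.2/5.7 = 1.263, and the noncentrality parameter is 1.263√n.

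| Patients in the test | Noncentrality | Probability of p < 0.05 |
|---|---|---|
| 10 | 3.99 | 0.943 |
| 23 | 6.06 | 0.9999 |
| 35 | 7.47 | > 0.999999 |
| 70 | 10.57 | 1.000 (all of 20,000 simulated trials) |

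In the same simulations, an independent two-sample t-test of the gains rejected in 4.9% of trials with 70 per cohort and in 4.8% with 35 per cohort, close to the nominal 5%.

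The result depends on how much patients recover regardless of the model. For smaller gains (assumed, same SD), the within-cohort test is significant with this probability:

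| Assumed gain | n = 35 | n = 70 |
|---|---|---|
| 3.6 | 95.2% | 99.9% |
| 2.0 | 52.3% | 82.5% |

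Even the smallest is about ten times the nominal 5% (52.3/5 = 10.5).

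**Step 3. Reading B: a paired test between cohorts.** This would need each usual-care patient to be linked to a PCRM-CI patient. The cohorts are recruited one after the other, and the article describes no matching. There are no pairs, so the test is not defined for this contrast.

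**Step 4. Does the correct contrast need more patients?** For the planned difference of 4.9 (SD 5.7), the independent two-sample t-test has 99.9% power with 70 per cohort and 94.4% with 35 per cohort. The difference detectable with 80% power is 2.7 points with 70 per cohort and 3.9 with 35. The planned size is ample, and combining the sites gives the more precise estimate.

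**The case against.** The strongest reply is that this is a slip of wording. A change score is already discharge minus admission, so comparing change scores by cohort may well mean comparing them between cohorts, with the test misnamed. The Sample size section supports this: it names a two-sided t-test for this contrast and says that the size follows from the methods to be used. This stands to the extent that the sentence is ambiguous, and one cannot assert that the authors meant to test recovery. It does not rescue the sentence, because a paired test is invalid on that reading too and the conflict with the sample size remains. The separate comparison of programs under Objective #2 also makes the within-cohort reading of Objective #1 a natural one.

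A reader might infer three stronger things that the article does not support.
- *That no comparison with usual care is planned.* One is, under Objective #2, and a regression is planned as secondary. The fault lies in which analysis is attached to the primary objective and how it is named.
- *That the study will declare success on a within-cohort test.* The article states no such decision rule. The near-100% figure describes how that test behaves under Reading A; it is not the trial's false-positive rate.
- *That analysis of covariance is required to cure the error.* An independent-groups comparison of gains is enough and fits the stated endpoint and sample size. A claim of efficiency for covariance adjustment would rest on assumed correlations, equal variances and balanced admission scores. This non-equivalent design does not assure balance, since admission criteria were revised between the cohorts (Data collection section).

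A separate analysis plan may hold more detail, but that does not answer the point: the article states a specific test, and it is the wrong one.

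**Conclusion.** The point holds: the test named for the primary objective is wrong as written, and the Sample size and Data analysis sections contradict each other. Within cohorts, it would be significant almost always with 23 or more patients at the protocol's usual-care gain, whether or not PCRM-CI helps. Between cohorts, it cannot validly be applied. Which of the two was meant cannot be settled from the article, and the conclusion does not depend on it.

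The figures rest on the protocol's planning values and on approximately normal gains; the results for 35 patients also assume an equal split by site. The finding concerns the primary test only. It does not say that the information needed to answer the question is missing. It should be corrected before analysis, because it determines what is reported as the primary result.

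**What to change.** Replace the sentence under Objective #1 with wording such as: *The primary analysis compares the mobility gain score (discharge minus admission FIMM) between the PCRM-CI and usual care cohorts, both sites combined with site as a factor. The result is the difference, PCRM-CI minus usual care, with its 95% confidence interval, from an independent-groups test or the equivalent linear model. Within-cohort changes are presented as description only.*

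Move the comparison of mobility gains at discharge from Objective #2 to Objective #1, and keep the site-specific results as supporting information.

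Because admission criteria were revised between cohorts to admit more patients with cognitive impairment, report the already planned regression beside the primary result. It should give the cohort coefficient adjusted for admission FIMM, site, cognitive impairment status and other baseline factors already collected. With admission FIMM in the model, the cohort coefficient is the same whether the outcome is the gain or the discharge score, so the endpoint is unchanged.

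The cost is small: no new data and no more patients. It is nevertheless a change to the stated primary analysis at a time when data on all 70 usual-care patients have been collected and 45 intervention patients are enrolled. It should be a dated amendment, with the reason given, made before outcomes are compared between the cohorts.

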### Setting and sample

The study is being conducted in two in-patient rehabilitation units at community rural sites. Site A is a 40-bed MSK rehabilitation unit in a 500-bed community hospital located 45 miles east of a large urban area. Site B is a 20-bed MSK rehabilitation unit at a small 120-bed community hospital. Ethics approval was obtained from both research sites and from Toronto Rehabilitation Institute.

The patient inclusion and exclusion criteria are: a) 65 years or older, b) admitted to rehabilitation directly from an acute care hospital after receiving surgery for a hip fracture; c) living in the community in a private home or residential setting (where an individual has services and supports but does not require 24 hour nursing care) prior to sustaining the hip fracture, d) able to speak and understand English; and e) have a family member or close friend who is familiar with the patient's pre-fracture condition and can act as a collateral informant. The patient exclusion criteria are: a) a pathologic hip fracture; b) a hip fracture associated with multiple trauma; and c) a previous hip fracture. All nursing staff, administrators and therapists caring for patients on the selected units will be invited to participate to assess their perceptions of the PCRM-CI. Written informed consent is obtained from both the patient and the caregiver/collateral informant at the first meeting following admission.

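### Cohort comparisons are set out for each site with no pooled, site-adjusted effect named, so one question gets two answers; mobility keeps its power within sites, return to the community does not

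*Protocol article*

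**What the plan says.** The primary and secondary objectives each ask a single question: whether the model improves mobility, physical function and return to the previous living situation. None is framed by site.

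Under Sample size, the calculation is for two whole groups. For mobility gain, "the sample size estimate is 23 patients with an alpha of 0.05, power of 80% and a two sided" t-test. For return to the community it gives 39 per group. The target is then 70 per cohort, 140 in all. Site does not enter either calculation.

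Under Data analysis, the level changes. For Objective #1, change scores go into paired t-tests within each cohort and site. For Objective #2 (1 & 2), usual care is compared with PCRM-CI "to assess the relative impact of the PCRM-CI model on outcomes for each site". For living situation, "Cross tabulations will be employed to assess rates of return to residence by rehab program and site". Mean gains of patients with and without CI are also compared by program and site. A multivariate regression is listed as secondary under both headings; it carries no by-site restriction, but it names neither cohort nor site.

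**The concern.** The unit of inference in the objectives and sample size (the cohort) is not the unit in the stated comparisons (the cohort within a site). If the two sites disagree, the text does not say which result answers the objective or how the two combine. Splitting the patients also costs precision, and the sample size was not set with that in mind. The sites differ in size: Site A has 40 beds, and "Site B is a 20-bed MSK rehabilitation unit at a small 120-bed community hospital". The smaller site could therefore carry a comparison with far fewer patients than the calculation assumes.

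**Working it through.** **Inputs (Sample size).** Mobility: usual care is assumed to gain 7.2 points on average; for the intervention cohort the assumption is that "the mean mobility gains score for the PCRM-CI group will be 12.1, with a common standard deviation of 5.7". Difference 12.1 − 7.2 = 4.9; standardised 4.9 / 5.7 = 0.86. Return to the community: 80% in the pilot for patients with CI, a level assumed to hold under PCRM-CI, against roughly 50% under usual care. Two-sided alpha 0.05 (the article states two-sided for mobility; taken as two-sided for the proportions).

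**Reproducing the plan's figures.**
- Mobility: n = 2(1.960 + 0.842)² / 0.86² gives 22 per group by the normal formula. The noncentral t solution is 22.2, so 23. Matches, read as per group.
- Return: n = [1.960√(2 × 0.65 × 0.35) + 0.842√(0.25 + 0.16)]² / 0.30² = (1.322 + 0.539)² / 0.09 = 38.5, so 39. Matches.

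**Assumed split by site.** The article gives beds, not accrual by site. Two splits of 70 per cohort are shown: even (35/35) and by beds 40:20 (47/23).

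**Power at n per cohort.** Mobility uses the noncentral t with 2n − 2 degrees of freedom and noncentrality 0.86√(n/2). Return uses Φ[(0.30√n − 1.322) / 0.640]. For example, at n = 35: (1.775 − 1.322) / 0.640 = 0.707, so 76.0%.

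| Patients per cohort | Mobility | Return |
|---|---|---|
| 70 (pooled) | 99.9% | 96.8% |
| 35 (each site, even) | 94.4% | 76.0% |
| 47 (Site A, by beds) | 98.5% | 87.4% |
| 23 (Site B, by beds) | 81.4% | 57.2% |

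With the article's 8% loss, 70 becomes 64 (pooled: 99.8% and 95.4%), 35 becomes 32 (92.3% and 72.1%) and 23 becomes 21 (77.6% and 53.3%). That loss was observed at 6 months in the control cohort, not at discharge.

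**Chance that exactly one site is significant when the assumed effect holds at both** (sites independent).
- Return, even: 2 × 0.760 × 0.240 = 36%. By beds: 0.874 × 0.428 + 0.126 × 0.572 = 45%.
- Mobility: 11% even, 20% by beds.

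**Patients needed for 80% at each site.** Return: 39 per cohort per site, so 39 × 2 × 2 = 156 before attrition, against 140 planned. Mobility: 23 × 2 × 2 = 92, within the 140.

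**CI patients by site.** The Background gives 31% to 65% with dementia and/or delirium among older orthopedic patients. This is assumed to apply here and equally in both cohorts.

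| Site size per cohort | CI patients | Mobility | Return |
|---|---|---|---|
| 35 (even) | 11 to 23 | 48% to 81% | 31% to 57% |
| 47 (Site A, by beds) | 15 to 31 | 62% to 92% | 40% to 71% |
| 23 (Site B, by beds) | 7 to 15 | 32% to 62% | 21% to 40% |

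**The case against.** Five points can be made for the plan.

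- **The primary outcome is adequately powered within sites.** This stands. A reader might infer that the site comparisons in general lack the stated power, but the plan's own inputs do not support that. For mobility in all patients, both sites keep 80% under either split before loss. Even the chance that both are significant is 0.944² = 89% (even) or 0.985 × 0.814 = 80% (by beds). Only a 23-patient site after 8% loss dips, to about 78%.
- **Not every analysis is by site.** This also stands. The secondary regression has no site restriction and may well be pooled. It is not a clear remedy, because it is labelled secondary and does not name the cohort effect or site.
- **No error rate is inflated as written.** A reader might infer that the false-positive rate nearly doubles. Counting success at either site would give up to 1 − 0.95² = 9.75%, but the protocol states no such rule. For the between-cohort comparisons it names no site-level test either.
- **Site results are intended.** The design section justifies two sites by the contrasts they allow, and one study aim is replication in different facilities. That supports reporting site results. It does not support leaving the overall estimate unnamed.
- **This is a condensed article.** Covariate lists and rules for combining sites often sit in an analysis plan, so their absence alone would be no finding. Here, however, the article does state the level of comparison, and it does not match the objectives or the sample size.

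The CI figures are the softest. The prevalence range comes from a broader population, and the Data collection section says admission criteria were widened between cohorts, so equal CI numbers are doubtful.

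**Conclusion.** The point holds in limited form. The stated cohort comparisons are by site, no pooled site-adjusted cohort effect is named, and two site results can differ with no stated way to combine them.

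The power cost is confined to return to the community, where at least one site is below 80% under either split, and to most by-site comparisons of CI patients. The CI exceptions are mobility at the 65% end, with an even split or at Site A by beds. The primary mobility comparison in all patients is not underpowered within sites before loss.

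These sizes rest on the plan's own effect assumptions, on an assumed split by site, and, for CI patients, on the assumed prevalence.

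**What to change.** State one pooled between-cohort comparison per outcome, adjusted for site, as the test of each objective:

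- ANCOVA with cohort, site and the admission score for the FIM mobility and locomotion score and for the motor-FIM.
- Logistic regression with cohort and site, or a Mantel-Haenszel analysis stratified by site, for return to residence.

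Keep site-specific estimates with 95% confidence intervals and a site-by-cohort interaction as secondary results; this still serves the stated interest in contrasts between sites. Treat comparisons of CI patients the same way: pooled and site-adjusted first, site detail second.

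The cost is analysis wording only, with no new patients or data. With 45 of 70 intervention patients accrued at the time of writing, the change could be made before the data are complete. The one loss is that site results no longer have confirmatory status.
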